### Randomization

#### Randomization Procedures

Participants will be randomly assigned using the Random Allocation Software (version 2.0; developed by Mahmood Saghaei, Isfahan University of Medical Sciences) to either the intervention group (plant-focused dietary intervention) or the control group (standard renal dietary intervention) [20]. The software will generate allocation codes (1 for intervention and 2 for control) based on block randomization with a 1:1 ratio and a block size that is a multiple of 4. This study is unblinded, and the allocation sequence will be accessible to the researcher assigning participants.

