## Methods

### Study Design

#### Overall Study Design

This study is an unblinded, open-label, parallel-group randomized controlled trial evaluating the effect of a plant-focused diet on the nutritional status of malnourished patients undergoing PD. This study will be conducted over 6 months, alongside each participants’ routine PD clinic visits. Patients and the public were not involved in the design, conduct, reporting, or dissemination plans of this study.

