#### Research Flow

This study protocol is adapted from a similar ongoing clinical trial involving patients with CKD with diabetes mellitus in the United States [16]. Figure 1 shows a diagram outlining the research flow. The study begins with participant screening, recruitment, and baseline assessment conducted on the same day. Following baseline assessment, participants are then randomized into either the intervention group receiving a plant-focused dietary intervention or the control group receiving a standard renal dietary intervention.

A 2-week familiarization phase is implemented immediately after randomization as part of the intervention period. During this phase, participants begin following their assigned dietary intervention and receive additional guidance and closer monitoring to support early adaptation and adherence. This phase is intended to facilitate understanding of the dietary protocol and to identify and address potential challenges early, rather than to assess eligibility or introduce selection bias.

Participants from both groups are instructed to continue the assigned dietary intervention for 6 months. Key outcome assessments are conducted at baseline (0 months), midpoint (3 months), and end line (6 months). Data collected will be analyzed for subsequent report writing and publication.

The intervention and study procedures, including screening, recruitment, data collection, and intervention delivery, will be conducted by a registered dietitian. Health care staff at the study site will assist with clinical procedures such as blood collection.

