### Recruitment

#### Study Population

Participants will be recruited from the nephrology unit at a tertiary care hospital in Klang, following approval from the research ethics committee. A second center may be considered to meet recruitment targets.

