#### Sample Size

The sample size was calculated using the standard formula for comparing 2 independent means in a parallel-group design using several assumptions.

On the basis of previous studies in dialysis populations, an estimated SD of 5 g/L was used to account for heterogeneity and to avoid underestimation of sample size. Notably, studies by Kalantar-Zadeh et al [17] and Rambod et al [18] reported serum albumin SDs ranging from 1.9 to 4.4 g/L, while a study by Limwannata et al [19] reported an SD of 5.0 g/L.

A clinically meaningful difference (δ) of 3 g/L (0.3 g/dL) was selected as it is consistent with differences in serum albumin levels observed across dialysis populations in previous studies. For instance, variations of 0.3 to 0.4 g/dL are observed between cohorts reported in studies by Rambod et al [18] and Limwannata et al [19]. Additionally, serum albumin is a well-established predictor of morbidity and mortality in patients undergoing dialysis, and even modest changes are considered clinically relevant in reflecting improvements in nutritional status [17].

Using the formula mentioned below, a 2-sided significance level of.05 (Zα/2=1.96) and 80% power (Zβ=0.84) were used to calculate the sample size. As a result, a minimum of 44 participants per group was required. After accounting for an anticipated 10% dropout rate, the sample size was rounded up to 50 participants for each group, with a total sample size of 100 participants. As repeated measurements will be conducted at baseline, 3 months, and 6 months, the calculated sample size is considered conservative.

The sample size was calculated using the standard formula for comparing 2 independent means in a parallel-group design, as shown below:

[figure not shown]

Where n is the sample size per group, Zα*/*2 is the standard normal deviate for a 2-sided significance level (1.96 for *α*=.05), Zβ is the standard normal deviate for power (0.84 for 80% power), σ is the SD, and δ is the expected difference between groups.

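### A single block size in an open-label trial leaves assignments predictable from earlier ones even once the list is concealed; vary the sizes and conceal the list together

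*Protocol article*

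**What the plan says.** Under Randomization Procedures, the protocol article says that software will generate the codes "based on block randomization with a 1:1 ratio and a block size that is a multiple of 4". The wording is singular. It gives no number, does not say that sizes vary, and mentions no stratification. The same paragraph adds: "This study is unblinded, and the allocation sequence will be accessible to the researcher assigning participants".

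Three other places bear on this:
- Overall Study Design: "This study is an unblinded, open-label, parallel-group randomized controlled trial".
- Research Flow: the study procedures, "including screening, recruitment, data collection, and intervention delivery, will be conducted by a registered dietitian". Screening, recruitment and baseline assessment fall on one day, and randomization follows.
- Study Population: one hospital is planned, and "A second center may be considered to meet recruitment targets".

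Under Participant Screening and Recruitment, candidates are found in the clinic registry, phoned, and booked for a visit. Study Timeline reports 9 participants recruited at submission.

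**The concern.** In a permuted block, once one arm has used its places, every remaining place belongs to the other arm. Someone who knows the block size and the past assignments can therefore name some coming assignments without seeing the list. Here the role that recruits also delivers the diets, so it learns past assignments in the ordinary course of work. With one planned center and no stated strata, there appears to be a single sequence to count.

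The recruiting role also controls who is phoned and when the visit is booked. If the next assignment is known, the choice or timing of candidates can follow it. That is selection bias in the comparison of albumin change. The planned adjustment for age, sex, dialysis duration and baseline nutritional status would not remove steering on motivation, appetite or expected adherence.

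**Working it through.** **Trial size.** The Sample Size section assumes a difference of 3 g/L, and "an estimated SD of 5 g/L was used" with "a 2-sided significance level of.05 (Zα/2=1.96) and 80% power (Zβ=0.84) were used". Then n = 2 × 5² × (1.96 + 0.84)² / 3² = 43.56, so 44 per group. Allowing for 10% dropout, 44 / 0.9 = 48.9, so 49, which the protocol rounds up to 50. These figures reproduce. N = 100 and the 3 g/L target are used below.

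**Share certain from earlier assignments, size known.** Let the block size be b = 2m at 1:1. The forced assignments are the final run of identical codes. Given the last code, the other m − 1 codes of that arm fall at random into the m + 1 gaps around the m codes of the other arm. The expected final run is 1 + (m − 1)/(m + 1) = 2m/(m + 1), so the expected share is 1/(m + 1).

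| Block size | Certain per block | Share | Best-guess accuracy |
|---|---|---|---|
| 4 | 4/3 | 33.3% | 70.8% |
| 8 | 8/5 | 20.0% | 66.6% |
| 12 | 12/7 | 14.3% | 64.3% |
| 16 | 16/9 | 11.1% | 62.8% |

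Full enumeration of the balanced blocks gives the same shares. For blocks of 4, best-guess accuracy is (1/2 + 2/3 + 2/3 + 1)/4 = 70.8%, against 50% by chance.

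In simulated trials of 100, the mean certain share is 33% for blocks of 4 (95% range 29% to 38%). It is 19% for blocks of 8 and 14% for blocks of 12, where the last block is cut short. A single block can reach 50%.

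**Can the size be inferred?** Assume an observer who gives 4, 8 and 12 equal prior weight.
- If the true size is 4, the likelihoods after 24 participants are (1/6)⁶, (1/70)³ and (1/924)². Size 4 then has probability 84%. After 48 participants it has 98%.
- If the true size is 8, a block looks like two balanced blocks of 4 with probability 6 × 6/70 = 0.514. Size 4 is ruled out within 24 participants with probability 1 − 0.514³ = 86%.

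**Randomly varying sizes.** Assume an observer who knows the set of sizes but not the size of each block. Simulated certain shares are about 7% for sizes 4 and 8, about 3% for 4, 8 and 12, and about 2% for 4, 6 and 8. Best-guess accuracy for 4, 6 and 8 is about 68%.

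**Illustrative bias (assumed).** Certain places split evenly between the arms on average. If the candidates steered to the two arms in those places differ by D in expected albumin change, the bias is share × D. The documents give no value for D; a range of 1.5 to 3 g/L is assumed.
- Blocks of 4: 0.333 × 1.5 = 0.5 g/L, to 0.333 × 3 = 1.0 g/L.
- Blocks of 8: 0.20 × 1.5 = 0.3 g/L, to 0.20 × 3 = 0.6 g/L.
- Blocks of 12: 0.143 × 1.5 = 0.2 g/L, to 0.143 × 3 = 0.4 g/L.

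These figures assume that every certain place is steered successfully.

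**The case against.** The strongest objection is that, as written, block counting adds nothing for the assigning researcher, who can see the sequence. That is right. Open access is the larger defect, and predictability from blocks is what would remain after it is cured. This is why the two changes belong together.

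Second, the article does not state the size, and a condensed article may leave the number to the full protocol. Not printing it is no error. A reader might infer that a third of assignments are known to be predictable, but the text supports this only if the size is 4. Nor is a third a ceiling: it is the average for blocks of 4. What stands is that the wording describes one size, restricts it to multiples of 4, and says nothing about variation.

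Third, a reader might infer that one person recruits, assigns and treats. The documents name a registered dietitian for recruitment and delivery and a researcher for assignment, and do not say that they are the same person. The point needs only that the recruiting role learns past assignments.

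Fourth, varying sizes hardly reduce best guessing: about 68%, against 71% for fixed 4, 66% for fixed 8 and 64% for fixed 12. This stands in full. The gain is in certainty, not in guessing.

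Fifth, a reader might take 1.0 g/L as the expected bias. It requires opposite steering of 1.5 g/L in each arm, a gap as large as the whole target difference, in every certain place. Nothing in the documents shows that steering has happened or will.

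**Conclusion.** The point holds as a worthwhile improvement, secondary to open access to the sequence. If the block size is fixed and is known or inferred, about 33% (size 4), 19-20% (size 8) or 14% (size 12) of assignments would on average be certain from earlier ones, even with the list concealed. This rests on a single unstratified sequence and a recruiting role that learns past assignments; the documents point to both. It also rests on a constant block size, which is the natural reading of the wording but is not confirmed. The size of any bias cannot be derived from the documents.

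**What to change.** Make both changes in Randomization Procedures, for participants still to be randomized:

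1. Replace the accessibility sentence with, for example: *The sequence will be held by a person who does not screen, recruit or deliver the diets. Each assignment will be released only after consent, eligibility and baseline data are recorded.*
2. Replace the block-size clause with, for example: *Permuted blocks of randomly varying size (for example 4, 6 and 8) will be used. The sizes and their order will not be disclosed to anyone who screens, recruits or delivers the diets until enrolment closes.*

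The second change does little without the first.

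**Cost.** No extra patients or visits are needed, but recruitment has begun, so a new list must be generated and the change documented. If all 9 participants recruited at submission had been randomized, a block was part-used whatever its size, since 9 is not a multiple of 4. The new list should start after the block that is open at the time of the change.

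Final arms may differ by a few participants. With a largest block of 8, the worst cut leaves a difference of 4, or 52 against 48. Then 1/52 + 1/48 = 0.04006, against 2/50 = 0.04000 with equal arms, so the loss of power is negligible.

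### The allocation sequence is open to the researcher who assigns participants, and no concealment from the person who recruits is described

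*Protocol article*

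**What the plan says.** Under Randomization Procedures, allocation codes are produced by software using "block randomization with a 1:1 ratio and a block size that is a multiple of 4". The same paragraph ends: "This study is unblinded, and the allocation sequence will be accessible to the researcher assigning participants".

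Under Research Flow, staffing is described as follows: "The intervention and study procedures, including screening, recruitment, data collection, and intervention delivery, will be conducted by a registered dietitian". Site health care staff help with clinical tasks such as taking blood. The section also places randomization after the baseline assessment.

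Under Participant Screening and Recruitment, candidates are found in the PD clinic's registry, checked against medical records, telephoned, and scheduled for a clinic visit at which written consent is taken.

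Under Ethics Approval, no data monitoring committee and no formal external monitoring are planned. Study Timeline reports 9 participants recruited at submission, out of a planned 100.

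**The concern.** Blinding and allocation concealment are separate safeguards. Blinding governs what is known after assignment, and two diets cannot readily be masked. Concealment governs what is known before assignment, and any trial can have it, including an open-label one. The protocol gives up the second safeguard without needing to.

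If the person deciding whom to call and when to book knows the next code, patients thought more willing or better placed to follow one diet can be brought in when that arm is due. The arms would then differ in prognosis before treatment starts, and the primary comparison of albumin change would mix that difference with the effect of diet.

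**Working it through.** **1. The relevant statements side by side**

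| Question | What the protocol article gives | Status |
|---|---|---|
| Who can see the sequence? | The researcher assigning participants (Randomization Procedures) | Stated |
| Who screens and recruits? | A registered dietitian (Research Flow) | Stated |
| Is the assigner the recruiter? | Assignment is not in the dietitian's list, but the list is open-ended and no other person is named | Inferred |
| When can the sequence be seen? | No timing is given | Inferred: nothing limits it to after enrolment |
| What keeps it from the recruiter? | No envelopes, central service or independent list holder is described | Not described |
| When is assignment made? | After baseline assessment (Research Flow) | Stated |

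**2. Where foreknowledge could act.** Several entry criteria are recorded or measured: albumin below 40 g/L, at least 6 months on PD, Kt/V, recent hospitalization, recent surgery. These leave limited room for discretion. The telephone contact and the scheduling of visits are different. The order in which eligible patients are called and booked is not fixed, and with a known sequence that order is enough to choose the arm.

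**3. The plan's own figure.** With SD 5 g/L, difference 3 g/L, two-sided 5% and 80% power:

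n = 2 × [5 × (1.96 + 0.84) / 3]² = 43.56, rounded up to 44 per group. With 10% dropout, 44 / 0.90 = 48.9, rounded up to 49; the protocol takes 50. The figure reproduces. It is used below only as a scale.

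**4. Illustration on assumed inputs.** Suppose a fraction f of each arm is exchanged and the exchanged patients differ by g in expected 6-month albumin change. One arm's mean rises by f × g and the other's falls by f × g, so the contrast shifts by b = 2 × f × g. Neither f nor g is in the documents.

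- f = 0.10, g = 3 g/L: b = 2 × 0.10 × 3 = 0.6 g/L, which is 0.6 / 3 = 20% of the target difference.
- f = 0.20, g = 3 g/L: b = 2 × 0.20 × 3 = 1.2 g/L, which is 40% of the target.
- The shift is proportional to g. With g = 1.5 g/L the two values halve to 0.3 and 0.6 g/L.

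For the effect on the test, take 50 × 0.90 = 45 completers per arm and SD 5 g/L. Then SE = 5 × √(2/45) = 1.054 g/L. If the diets do not differ, the two-sided rejection rate is 1 − Φ(1.96 − b/SE) + Φ(−1.96 − b/SE):

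| b (g/L) | b/SE | Rejection rate |
|---|---|---|
| 0.3 | 0.28 | about 6% |
| 0.6 | 0.57 | about 9% |
| 1.2 | 1.14 | about 21% |

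This is a simple two-mean approximation without covariate adjustment.

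**5. What the planned analysis could recover.** Statistical Analysis plans intention-to-treat and adjustment for factors such as age, sex, dialysis duration and baseline nutritional status. Intention-to-treat does not help, because the imbalance would arise before assignment. Adjustment could absorb part of an imbalance in measured factors, but not one in motivation or expected course. Taking albumin from hospital laboratory records limits measurement bias but has no bearing on who enters each arm.

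**The case against.** The strongest reply is that someone must operate the list. The protocol says only that the assigner has access. If the assigner is not the recruiting dietitian, the sentence is compatible with concealment from the recruiter, and a fuller protocol might say so. This stands in part: the same-person link is an inference and must be labelled as one. It does not remove the point, because the article states open access outright and describes nothing that separates the two roles.

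Several stronger readings are tempting and are not supported:

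- A reader might infer that the article says the next code is visible before a patient is approached. It gives no timing of access.
- A reader might infer that randomization is broken or that enrolment has been steered. The sequence is still computer-generated and blocked, and the text shows only vulnerability.
- A reader might infer that the open list is justified by the open-label design. The sentence joins the two facts and gives no reason.
- A reader might see same-day screening, recruitment and baseline as what makes steering easy. Doing these on one day shortens the interval between them; the opening lies earlier, in phoning and booking.
- A reader might fault the block size. A multiple of 4 does not fix one size, and block size is immaterial while the list itself can be read.

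It is also fair to say that the illustration is not evidence of size. Its 3 g/L gap is the trial's target difference, borrowed as a scale.

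**Conclusion.** The point holds as a design weakness that should be corrected before further enrolment. The sequence is accessible to the assigner, no concealment from the recruiter is described, and the way candidates are contacted would let foreknowledge decide the arm. That the recruiter has this foreknowledge is the natural reading of two sections taken together, not a stated fact.

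The size of any bias cannot be computed from the documents. The 0.6 to 1.2 g/L shift rests wholly on assumed inputs, and covariate adjustment could reduce it to an unknown degree. The reason to act is that the analysis cannot fully repair selection on unmeasured factors, while a procedural change can prevent it for those still to be enrolled: 100 − 9 = 91 participants as of submission, fewer if recruitment has continued.

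**What to change.** Replace the last sentence of Randomization Procedures. The new text should say that, for participants not yet enrolled:

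- a fresh sequence is generated and held by an existing team member who does not screen or recruit;
- assignments are kept in sequentially numbered, opaque sealed envelopes, or in an equivalent tool if one exists;
- each assignment is released only after consent, eligibility and baseline data have been recorded.

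The order of steps in Research Flow already places randomization after baseline, so only the custody and release of the sequence change. The protocol should also state who assigns participants and how those already enrolled were allocated.

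Add to Statistical Analysis a sensitivity analysis of the primary outcome that excludes participants enrolled under the accessible sequence (9 at submission, more if recruitment has continued). The primary analysis stays on all randomized participants.

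The cost is one protocol amendment and minor administrative work. This assumes that a non-recruiting team member is available, which the documents do not confirm. No change to sample size is needed.

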#### Intervention Group vs Control Group

The control group will follow a standard renal diet and be encouraged to maintain their usual dietary and physical activity patterns, with guidance to ensure that at least 50% of their total protein intake comes from high biological value animal-based sources. The standard renal diet was chosen as comparator as it reflects the current clinical practice. In contrast, the intervention group will follow a plant-focused dietary pattern that emphasizes plant-based foods, such as fruits, vegetables, legumes, whole grains, nuts, seeds, and plant oils, with minimal reliance on animal-based products. Participants in the intervention group will be required to consume plant-focused meals for most of their daily meals. For example, those consuming 3 meals per day must ensure that at least 2 out of the 3 meals are plant based, while those consuming 4 meals per day must ensure that at least 3 out of the 4 meals are plant based. The remaining meal or snack may include either plant- or animal-based foods to support flexibility and adherence.

Participants in both groups will receive individualized dietary counseling at each data collection point (baseline, 3 months, and 6 months). In addition, participants are also provided with educational pamphlets and 14-day structured meal plans that incorporate natural food sources and culturally appropriate meal choices. Meal plans for both groups are developed in accordance with the Malaysian Medical Nutrition Therapy Guidelines for Chronic Kidney Disease and the Kidney Disease Outcomes Quality Initiative Clinical Practice Guidelines for Nutrition in CKD [7,21]. Throughout the study, participants will continue to receive standard medical care, with no specific concomitant care prohibited.

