**Methods:**

This is an unblinded, open-label, parallel-group randomized controlled trial conducted at a tertiary care hospital in Klang. A total of 100 adult outpatients undergoing PD will be recruited and randomized (1:1) to receive either a plant-focused diet emphasizing plant-based proteins or a standard renal diet emphasizing animal-based proteins for 6 months. Both interventions will be individualized to meet nutrient requirements and delivered through dietitian-led counseling, educational materials, and regular follow-ups. Data will be collected at baseline and after 3 and 6 months of intervention. Parameters assessed include sociodemographic characteristics; anthropometric and biochemical measures (renal, glucose, lipid, and inflammatory profiles); malnutrition inflammation score; dietary adequacy; physical activity and function; quality of life; and knowledge, attitude, and practices of renal diet. Baseline data will be analyzed using descriptive statistics, with independent *t* tests (2-tailed) or Mann-Whitney *U* tests for between-group comparisons. Changes across time points will be analyzed using a generalized linear model for repeated measures, with Bonferroni adjustment for multiple comparisons. Analyses will be adjusted for confounders with significance set at *P*<.05. Ethics approval has been obtained from the Universiti Kebangsaan Malaysia Research Ethics Committee (JEP-2025-812).

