Despite its benefits, PD is associated with various complications, particularly malnutrition and protein-energy wasting. A systematic review and meta-analysis reported that patients undergoing PD have the highest global prevalence of malnutrition at 45.3%, compared to 43.1% in patients undergoing hemodialysis and 38.5% in nondialysis individuals [4]. The 31st Report of the Malaysian Dialysis and Transplant Registry indicated a widespread malnutrition among patients undergoing PD in Malaysia, with only 27% of patients undergoing PD in half the centers meeting both the recommended body mass index (BMI) and serum albumin targets in 2023 [3]. Additionally, 48% were overweight or obese (BMI≥25 kg/m²), while 8% were underweight (BMI<18.5 kg/m²), highlighting the coexistence of overnutrition and undernutrition [3]. A study conducted among the dialysis population in Malaysia also found a high prevalence of malnutrition among patients undergoing PD, with >70% classified as malnourished across 3 different assessment criteria [5]. Macronutrient and micronutrient deficiencies in patients undergoing PD can result from factors such as inadequate dietary intake, impaired intestinal function, losses through dialysate and urine, metabolic imbalances, chronic inflammation, and the hypercatabolic state of ESRD [6-8]. Poor oral intake is a major contributor to malnutrition among this population. A study conducted in Malaysia reported that the average energy intake among patients undergoing PD ranged from 23 to 25 kcal/kg/day, with protein intake at approximately 0.82 g/kg/day, which are both below recommended levels [9]. Studies have shown that malnutrition in patients undergoing PD result in lower quality of life (QOL) and higher risks of morbidity and mortality [10-12]. Given the strong association between poor nutrition and adverse health outcomes, effective dietary strategies are essential. Therefore, further research is essential to improve nutritional strategies for disease management, ultimately improving patient outcomes and QOL.

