### Research Objectives

The primary objective is to determine the effect of a plant-focused dietary intervention on changes in serum albumin from baseline to 6 months compared with standard-of-care renal diet in malnourished patients undergoing PD.

The secondary objectives are (1) to determine the effect of a plant-focused dietary intervention on changes in anthropometric measurements (BMI, TSF, and MAMC), biochemical and inflammatory markers (lipid profile, hs-CRP, and renal parameters), dietary adequacy and nutrient intake, MIS scores, physical function and muscle strength, QOL, appetite scores, and dialysis adequacy from baseline to 6 months compared with standard-of-care renal diet in malnourished patients undergoing PD and (2) to determine the baseline nutritional status of malnourished patients undergoing PD, including their knowledge, attitude, and practices of renal diet intake, as well as sociodemographic characteristics and medical history.

Exploratory objectives are to assess adherence to a plant-focused dietary intervention over the 6-month period and to evaluate retention rates over 6 months of intervention.

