	**Protein source**					
		Control	<50% protein intake from HBV^b^ animal-based sources		≥50% protein intake from HBV animal-based sources	
		Intervention	<2/3 or 3/4 meals are plant-based food sources		≥2/3 or 3/4 meals are plant-based food sources	

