**Nutrient intake**						
	Total energy intake		Deviation of >+20% or −20% of target energy prescription		Within +20% or −20% of target energy prescription	
	Total protein intake		Deviation of >+20% or −20% of target protein prescription		Within +20% or −20% of target protein prescription	
	Total sodium intake		Outside 2000-3000 mg/day		Within 2000-3000 mg/day	
	Total potassium intake		Outside 2000-3000 mg/day		Within 2000-3000 mg/day	
	Total phosphate intake		Outside 0.8-1.0 g/day		Within 0.8-1.0 g/day	

^a^Total scores=0-7 (each daily dietary record is scored out of 7 points).

^b^HBV: high biological value.

**Table 3 table3:** Diet compliance score classification.

	Per day (1-day)	Per monthly review (3-day)	Per monthly review (3-day)
Maximum score	7	21	21
Total score	—^a^	<10.5/21 (<50%)	≥10.5/21 (≥50%)
Classification	—	Poor compliance	Adequate compliance

^a^Not applicable.

Each daily dietary record is scored out of a maximum of 7 points. A “1-day” record refers to a single 24-hour dietary record, whereas a “3-day” record represents the aggregation of three separate daily dietary records collected from participants. The total score for each 3-day dietary assessment therefore ranges from 0 to 21 points. Total scores are calculated by summing the scores from each daily record. A total score of ≥50% (≥10.5/21) indicates adequate dietary compliance, whereas scores <50% indicate poor compliance. To ensure feasibility and acceptability, the dietary compliance scoring system will be pilot tested with participants during the first 2 weeks of the study period.

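### Only the control arm is told to keep its physical activity unchanged, and the same phrase tells controls to keep their usual diet, at odds with the individualized diet set for both arms

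*Protocol article*

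**What the plan says.** The section Intervention Group vs Control Group assigns controls a standard renal diet. In the same sentence it says that they will be "encouraged to maintain their usual dietary and physical activity patterns", with guidance that at least half of their protein be of high biological value and animal origin. The description of the intervention arm covers the plant-focused pattern and how many daily meals must be plant based. It says nothing about physical activity.

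The other provisions on diet apply to both arms:

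- Abstract, Methods: "Both interventions will be individualized to meet nutrient requirements".
- Research Flow: "Participants from both groups are instructed to continue the assigned dietary intervention for 6 months".
- Intervention Group vs Control Group: "Meal plans for both groups are developed in accordance with the Malaysian Medical Nutrition Therapy Guidelines", alongside individualized counseling for everyone at baseline, 3 and 6 months.
- Table 2: energy and protein are scored against a prescription, the protein item as "Within +20% or −20% of target protein prescription", with no split by arm. The protein-source item is split; for controls it reads "≥50% protein intake from HBV animal-based sources".

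The secondary objectives include "physical function and muscle strength, QOL, appetite scores".

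**The concern.** A two-arm diet trial can attribute a difference to the diet only if the arms are otherwise told the same things. Here one phrase gives controls two instructions that the other arm does not get.

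**Activity.** Controls are encouraged to hold activity steady, while intervention participants are free to change it. Participants know their arm, and the dietitian who delivers the intervention also collects data. If activity drifted apart as a result, the Short Physical Performance Battery and handgrip results could reflect that as well as the diet.

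**Diet.** Encouraging a control to keep a usual diet does not fit with prescribing an individualized one. The Background section describes usual intake in Malaysian peritoneal dialysis patients as low, with "protein intake at approximately 0.82 g/kg/day, which are both below recommended levels". A control whose own intake is inadequate cannot both keep it and bring it up to a prescription, and the article does not say which instruction prevails.

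**Working it through.** The plan gives no figure on this point, so the check is a reading of the text with two small counts.

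**Step 1. Which instructions differ by arm?**

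| Provision | Control | Intervention | Same? |
|---|---|---|---|
| Diet individualized to requirements (Abstract) | yes | yes | yes |
| Assigned diet continued for 6 months (Research Flow) | yes | yes | yes |
| Counseling and 14-day meal plans, same guidelines | yes | yes | yes |
| Energy and protein scored against prescription (Table 2) | yes | yes | yes |
| Protein source or plant-based meals | animal, at least 50% | plant-based for most meals | no, by design |
| Keep usual diet | encouraged | not stated; meals must change | no |
| Keep usual physical activity | encouraged | not stated | no |

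The fifth row is the contrast that the trial is meant to test. The last two rows come from the single phrase at issue.

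**Step 2. How far does the compliance score treat the arms alike?** Table 2 has 7 items: meal frequency, protein source, energy, protein, sodium, potassium and phosphate. One is split by arm. Shared: 7 − 1 = 6, and 6/7 = 85.7%. This suggests that the authors meant the arms to differ in protein source and not in quantity. It therefore counts against a harmful reading of the diet half while confirming that the wording is out of line with the rest.

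**Step 3. Does the control sentence agree with itself?** Not for every patient. A control whose usual protein is less than half high biological value animal protein must change diet to meet the floor set in the same sentence.

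**Step 4. Would a divergence be seen?**

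- Diet: yes. Three-day food diaries are completed monthly, and Table 4 lists dietary adequacy as a secondary outcome tested by the time-by-group interaction.
- Activity: it would be recorded. Table 1 has a physical activity record at screening and at months 0, 3 and 6. Recording shows an imbalance but does not prevent one. Adjusting for activity measured after randomization would not cleanly restore the intended comparison, because the diet may itself affect activity.

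**Step 5. How many participants could still get corrected wording from baseline?** Planned 100, recruited 9 at submission: 100 − 9 = 91 at most, fewer as enrollment proceeds.

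**The case against.** The strongest case on the other side has three parts.

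1. **Context.** The control sentence opens by prescribing a standard renal diet and closes with the animal-protein floor. Between these, usual dietary patterns most naturally means customary eating that includes animal foods, set against the switch asked of the other arm. Controls plainly have prescriptions, because Table 2 scores them against one. This largely stands: the diet half is a fault of wording more than of design.

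2. **Activity.** Asking people to keep activity as it is asks for no change, and nothing tells the intervention arm to change. The full protocol or counseling script, which is not shown, may give both arms the same line. The first part is fair and limits the weight of the point. The second does not remove it, because the article states the instruction for controls and then contrasts the other arm without it. That is a stated asymmetry, not an omitted detail.

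3. **Consequence.** No effect on any outcome is shown. This stands.

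A reader might infer that controls are left on a deficient diet, so that the trial compares corrected with uncorrected intake and the albumin result is biased. The documents do not support this. The shared provisions point the other way, the low intake figures come from a separate cited study and not from this trial's controls, and a quantity difference would show in the diaries. One could assume an albumin shift and compute how often it would produce a false-positive result, but the shift would have no source in the documents.

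A reader might also infer that the intervention arm is encouraged to be more active. The text is silent on that.

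**Conclusion.** The point holds as a minor one. The one-arm activity instruction is a real and avoidable difference between arms, relevant mainly to physical function and muscle strength. The usual-diet phrase conflicts in wording with the individualized diet that both arms are meant to follow, but the shared provisions suggest that no difference in energy or protein quantity is intended. If counseling follows those provisions, the diet part has no practical effect and only the activity instruction remains.

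The conclusion assumes that the article's description reflects what participants are told. The size and direction of any bias cannot be derived from the documents. The sample size is unaffected, and there is no ground for saying that the primary albumin comparison is compromised.

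**What to change.** Amend the control description in Intervention Group vs Control Group in two ways:

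- Delete the encouragement to keep usual dietary patterns. Controls then follow the individualized standard renal diet, with at least 50% of protein from high biological value animal sources.
- Move the request to keep usual physical activity into a sentence that applies to both arms.

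Make the same change in the counseling script. No new measurement, analysis or sample size is needed, because intake and activity are already recorded in both arms.

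The cost is a wording amendment. Participants already counseled (9 at submission) would receive the corrected wording at their next contact, so their first weeks may have followed the present text. The control arm becomes slightly less like untouched usual care, but it remains the standard renal diet that the article chose because it reflects current practice.
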